# 1 Study overview

A major goal in the neurological rehabilitation of patients with severe disorders of consciousness is to enhance the arousal and ability of these patients to communicate.

To activate them and thus enhance their state of consciousness, patients are treated with multimodal stimulation. This stimulation consists of vestibular, auditory, tactile, olfactory, and visual inputs. To stimulate vestibular sensory information it appears to be essential to mobilize the patient into a vertical position. Although desirable, head-up tilt cannot always be easily realized in the early stages after brain injury when patients are still unconscious. A common problem is the occurrence of syncope due to central sympathetic dysfunction and the absence of the venous pump as a result of paralysis of the leg muscles.

In the past, head-up tilt was performed gradually over a period of several weeks, in order to stabilize the patient's circulatory system and prevent recurrent syncope. In clinical practice this is done with a tilt table. The Erigo is a tilt table with an integrated robotic stepping device, which was developed to combine the advantages of a classical tilt-table therapy with those of a passive-movement therapy.. It provides a feasible way of simultaneously inducing passive leg movements and gradually inclined head-up tilt in patients who are comatose or semi-comatose. Moreover, it was shown that patients with a traumatic spinal cord injury with similar vegetative dysfunctions could be mobilized faster by using such a device.

The aim of this study is to determine, if an Erigo therapy has an immediate stabilizing effect on the cardiovascular system and if it increases vigilance in the early stages of mobilization of patients with a severe brain injury. These effects will be compared with a standard tilt-table therapy.

Vegetative functions will be determined by measuring blood pressure and recording heart rate before, during, and after the intervention. Reactions on the Erigo will be compared with those of the standard tilt table. In addition, vigilance will be measured by means of the Coma Recovery Scale-revised.

This study consists of two separate experimental procedures. The first is a pilot study with a cross-over design, in which the patients will be verticalized once on the Erigo and once on the traditional tilt table. The second is a single-blind randomized controlled trial, in which the above-named parameters for circulation and vigilance will be examined over a 3-week period. A follow-up examination will be scheduled 3 weeks after the last therapy. We would like to test the hypothesis that patients show a better effect on vigilance after the Erigo therapy than the patients who receive a tilt-table therapy.

### 3 Introduction

A major goal in the neurological rehabilitation of patients in the vegetative or minimally conscious state is to enhance arousal and ability of the patients to communicate.

For decades patients have been treated with multimodal stimuli (vestibular, auditory, tactile, olfactory, and visual sensory inputs) to activate and thereby increase their state of consciousness. So far, there is no evidence that this treatment regimen enhances the rehabilitation outcome of patients ([1]).

However, some authors have reported changes in several parameters due to a stimulation, e.g., a significant change in heart rate and breathing rate during a tactile and auditory stimulation ([2]).

In general, the ascending reticular activating system (ARAS) plays an important role in activating energy for the entire brain and thus in any change in state of consciousness or the regulation of alertness and arousal. According to clinical experience mobilization into a vertical body position seems to play a crucial role in the enhancement of the patient's vigilance. Neurons in the reticular formation and thus in the ARAS receive an excitatory and inhibitory sensory input, especially of the vestibular system.

In the early phase after an acute brain injury, it is frequently difficult to mobilize a patient into a sitting position, much less into a standing position, because of circulation problems due to vegetative dysfunctions resulting from the prolonged bed rest. Since the fifties it has been a therapeutic measure to verticalize the patient by steps on the tilt table in order to stabilize the circulation. However, a successful adaptation of the blood pressure to changes of position, which allows the patients to sit longer in a wheelchair, is frequently only possible after a period of weeks. ([3]).

A disorder of circulatory regulation in acute paraplegics is similarly pronounced due to the suppression of the sympathetic system. These patients have so far been mobilized with the tilt table. Recent studies in paraplegics showed that both the passive movement of the leg muscles ([4]) as well as activation of the leg muscles by means of functional electrostimulation ([5]) increase the circulation parameters of stroke volume and heart rate. Therefore the Erigo was developed, in order to combine the advantages of the classical tilt-table training with those of a movement therapy that is simple to perform. This device makes possible a passive movement of the legs with a smoothly adaptable degree of verticality. It was shown that healthy test persons had a significantly lower rate of neurocardiogenic syncope during mobilization on the Erigo compared to the classical tilt-table therapy ([6]). A similar circulation-stabilizing effect can also be expected in patients with severe brain injury due to the reduction of venous pooling.

An earlier and longer mobilization in the course of rehabilitation and the simultaneous passive movement of the patients mean on the whole a faster mobilization and activation that hopefully finally leads to the more rapid achievement of the goal of rehabilitation.

## 4 Research question/Outcome criteria

### 4.1 Pilot study

The aim of the pilot study is to determine if patients in the vegetative or minimally conscious state potentially have a cardiovascular benefit from mobilization with the Erigo compared to therapy with a standard tilt table. The patient's circulation is expected to better adapt to the first verticalization, i.e., a prolonged mobilization in an extremely vertical position should be possible.

In addition, the state of consciousness will be examined to see if one therapy session on the Erigo can already improve the state of consciousness of the patients.

For this head control and muscle tone will be measured, as well as the reaction to a command. Further head control and muscle tone as well as a reaction to speech will be documented. In addition the efficacy of sensory stimuli will be measured by the changes in skin resistance and the variability of heart rate before and after therapy. The Coma Recovery Scale (CRS) will be applied during and after therapy.

If the above-described examinations can show that positive circulatory stabilization effects result from therapy on the Erigo, the mechanism underlying this success will be addressed in the next step. 'So far the neurological literature has assumed that passive leg movements already increase venous backflow to the heart ([4], [6]). It is, however, questionable from the internist's viewpoint, whether purely passive movements of a standing patient can lead to sufficient muscular pump action to prevent syncope.

A possible explanation is that spinal gait pattern generators are activated by means of the gait-similar movements on the Erigo and thus a reflexive, active co-movement of the patients' results ([7]). Therefore, a sample of treated patients will be examined using surface-EMG on different muscle groups of the leg to clarify if there is muscle activity during the Erigo therapy.

### 4.2 Randomized controlled trial

The same parameters will be collected in the randomized controlled trial as in the pilot study. We expect that a longer application of Erigo will have the result that the improved vigilance will be maintained after therapy is finished. Thus, the Coma Recovery Scale-Revised ([12]), as well as the skin conduction measurements and the heart rate variability will be collected before the intervention phase, and 3 and 6 weeks later. However, this will not be done during the interventions to ensure the blinding of the raters.

#### 4.2.1 Primary outcome measure

To evaluate a clinically relevant change in the level of consciousness due to the Erigo therapy compared to the tilt-table therapy the following parameter will be measured:

- Coma Recovery Scale-Revised assessed by experienced, blinded rater

#### 4.2.2 Secondary outcome measure

To evaluate an immediate stabilizing effect of the Erigo therapy on circulation, the following cardiovascular parameters will be measured:

- Heart rate
- Blood pressure; the Hypothesis: difference between initial value and the value after the intervention phase is greater for the tilt-table therapy (drop in blood pressure during tilt-table therapy)
- Oxygen saturation; the Hypothesis: increased oxygen saturation during Erigo therapy
- As co-variables the duration of verticalization (max. of 30 min per therapy session), and the degree of the maximum tilt will be analyzed

To evaluate a clinically unapparent effect on vigilance the following parameters will be measured:

- Skin conductance as reaction to command (should increase during Erigo therapy)
- Heart rate variability (should increase during Erigo therapy)
- Head control/movement during therapy (better during Erigo therapy)

The change in muscle tone or spasticity will be measured before the intervention, after the intervention, and after a 3 week follow-up period using the

- Ashworth-Scala.

To better compare the results of this study with results of international studies, the following parameters will be measured:

- at study onset: GCS (Glasgow Coma Scale)
- at discharge: GOS (Glasgow Outcome Scale)

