## 7 Study procedure

### 7.1 Procedure

| Erigo                                                                                                                                                                                           | Tilt table |
|-------------------------------------------------------------------------------------------------------------------------------------------------------------------------------------------------|------------|
| Attachment of ECG electrodes, blood pressure cuff, and pulsoxymeter for continuous measurement of pulse, ECG, blood pressure, and oxygen saturation; also for performance of first measurement. |            |
| Patient is transferred from bed/wheelchair to the Erigo or to the tilt table, is attached to it, and secured with a belt over the stomach.                                                      |            |

|                                                                                                                                                                                                                                                                                                |  |
|------------------------------------------------------------------------------------------------------------------------------------------------------------------------------------------------------------------------------------------------------------------------------------------------|--|
| The foot supports are adjusted to the individual length of the legs of the patients.                                                                                                                                                                                                           |  |
| Adjustment of range of leg movement to patient's maximally possible range.                                                                                                                                                                                                                     |  |
| Start of leg drive at a maximally tolerated speed (the goal is 40 steps/min or at least 20 steps/min) while patient remains in horizontal position.                                                                                                                                            |  |

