| Upright placement to 30 degrees; conditions maintained for about 5 min.                                                                                                                                                                                                                        |  |
| Subsequently the patient is uprighted to 50 degrees (if appropriate, with same drive parameters); if circulation is good, to 70 degrees.                                                                                                                                                       |  |
| At least 15-min-long or maximally 30-min-long therapy during the achieved angle of verticality. The duration of mobilization in the indicated time period is as long as possible, if there is no depression of the circulation and in agreement with the predetermined criteria (see below).   |  |
| At the end of therapy the Erigo or tilt table is lowered into the initial horizontal position by about 15 degrees, with a break for the patient to acclimatize him/herself. After the final measurement the apparatus is disassembled and the patient is transferred to the bed or wheelchair. |  |

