## 7.5 Non-invasive measures of randomized controlled study

| Measures                                                                                  | Time point                                           | Period  | Frequency |
|-------------------------------------------------------------------------------------------|------------------------------------------------------|---------|-----------|
| Screening exam administered to determine eligibility, incl. use of patient medical record | pre enrollment                                       | 6 weeks | 1x        |
| ECG                                                                                       | pre enrollment                                       | 6 weeks | 1x        |
| ECG monitoring                                                                            | during each therapy                                  | 6 weeks | 9x        |
| Heart rate                                                                                | during each therapy                                  | 6 weeks | 9x        |
| Blood pressure                                                                            | during each therapy                                  | 6 weeks | 9x        |
| Oxygen saturation                                                                         | during each therapy                                  | 6 weeks | 9x        |
| Skin response                                                                             | before therapy, 3 and 6 weeks after start of therapy | 6 weeks | 3x        |
| Heart rate variability                                                                    | before therapy, 3 and 6 weeks after start of therapy | 6 weeks | 3x        |
| Ashworth Scale                                                                            | before therapy, 3 and 6 weeks after start of therapy | 6 weeks | 3x        |
| Coma Recovery Scale-R                                                                     | before therapy, 3 and 6 weeks after start of therapy | 6 weeks | 3x        |
| Glasgow Coma Scale                                                                        | before start of therapy                              | 6 weeks | 1x        |
| Glasgow Outcome Scale                                                                     | at hospital discharge                                |         | 1x        |

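### The secondary blood pressure contrast compares the initial value with one taken after the intervention, although its hypothesis is a fall during upright tilt

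*Protocol*

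**What the plan says.** All references are to the protocol.

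- **Aim (4.2.2).** The cardiovascular measures are introduced with "To evaluate an immediate stabilizing effect of the Erigo therapy on circulation".
- **Blood pressure (4.2.2).** The hypothesis is "difference between initial value and the value after the intervention phase is greater for the tilt-table therapy (drop in blood pressure during tilt-table therapy".
- **Following bullet (4.2.2).** Oxygen saturation is timed differently: "the Hypothesis: increased oxygen saturation during Erigo therapy".
- **Overview (section 1).** Before, during and after are listed as separate times: "Vegetative functions will be determined by measuring blood pressure and recording heart rate before, during, and after the intervention".
- **Session procedure (7.1).** Monitoring is attached for "continuous measurement of pulse, ECG, blood pressure, and oxygen saturation", and a first measurement is listed at that step, ahead of transfer to the device. On the Erigo the leg drive starts "while patient remains in horizontal position". At the end the table is lowered to horizontal, "with a break for the patient to acclimatize him/herself. After the final measurement the apparatus is disassembled".
- **Schedule for the randomized trial (7.5).** Blood pressure is listed only during therapy. Skin response, heart rate variability, Ashworth Scale and CRS-R are set at "before therapy, 3 and 6 weeks after start of therapy".
- **Step-down (section 10).** A systolic fall of 20 mmHg, or a diastolic fall of more than 10 mmHg, on uprighting means that therapy continues at a lower angle.

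**The concern.** The blood pressure sentence fixes one time for the contrast and another for the effect. An orthostatic fall appears while the patient is upright and can recover once the patient lies flat. A contrast between two readings outside the upright phase may show little even if the devices differ clearly during tilt.

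Blood pressure is one of three cardiovascular outcomes (with heart rate and oxygen saturation) serving the circulatory aim. A null result on this contrast could be misread as no stabilization during verticalization. This is not a detail left open for an analysis plan: the protocol fixes a contrast, and an analysis that followed it literally would use the wrong reading.

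**Working it through.** The protocol attaches no figure to this outcome, so there is none to reproduce. The check is mainly of the text.

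**Step 1: what could the after-value be?**

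| Meaning of intervention phase | After-value in the protocol | Upright fall captured? |
|---|---|---|
| One session (fits the immediate effect in 4.2.2) | Final measurement in 7.1, named after the lowering and the break | No, if the order of the text is the order of events |
| The three-week period (the sense used in 4.2) | None: 7.5 lists blood pressure only during therapy | No; the contrast has no scheduled after-value |
| The upright part of a session | A reading once the patient has been lowered | No |

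**Step 2: is the initial value fixed?** Not firmly. The first measurement in 7.1 is listed with attachment of the monitoring, before transfer from bed or wheelchair, so its posture may differ from that of the final measurement. A baseline taken later, on the Erigo with the legs already moving, would include part of the treatment.

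**Step 3: are the right data available?** Yes. Continuous measurement is stated in 7.1 and readings during therapy in 7.5. The reading interval is not given.

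**Step 4: how much could be lost? Illustration only.** From the protocol come 20 mmHg, 22 patients per group, and 15 and 30 minutes. Every other input is an assumption.

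Let the upright systolic fall be normal with SD 12 mmHg and mean 15 (tilt table) or 8 (Erigo). With no curtailment the difference is 15 − 8 = 7 mmHg. As the opposite extreme, cut every fall at c = 20:

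E[min(X, c)] = μΦ(a) − σφ(a) + c(1 − Φ(a)), with a = (c − μ)/σ

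- Tilt table: a = 0.417; 15 × 0.6615 − 12 × 0.3658 + 20 × 0.3385 = 12.30
- Erigo: a = 1; 8 × 0.8413 − 12 × 0.2420 + 20 × 0.1587 = 7.00
- Difference: 5.30 mmHg

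If a fraction f of the fall persists at the horizontal reading, the stated contrast is f times the upright difference:

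| f | No curtailment (7 mmHg) | Hard cut at 20 (5.30 mmHg) |
|---|---|---|
| 0 | 0 | 0 |
| 0.10 | 0.70 | 0.53 |
| 0.25 | 1.75 | 1.33 |
| 0.50 | 3.50 | 2.65 |

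Power depends on a further assumption, the reading-noise SD s. The SD of the contrast is √((f × 9.56)² + s²), where 9.56 is the pooled SD of the cut falls (8.63 and 10.40). For a two-sided 5% t-test with 22 per group:

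| s (mmHg) | Lowest upright reading (f = 1) | Horizontal reading, f = 0.25 |
|---|---|---|
| 0 | 44% | 44% |
| 4 | 38% | 15% |
| 8 | 28% | 8% |

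Without noise, mean and spread shrink together and, for any f above 0, power does not change. No firm power loss can therefore be claimed.

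**Step 5: a check on the remedy.** A minimum falls as the window lengthens. In a simulated autoregressive series with one reading per minute, within-session SD 4 to 8 mmHg and autocorrelation 0 to 0.8, the expected minimum over 30 minutes lies 1.2 to 3.1 mmHg below that over 15 minutes with no true difference. Section 7.1 allows 15 to 30 minutes, so an unequal window would count against the arm that stands longer. This is a hazard of a minimum-based measure, not a fault in the protocol's contrast.

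**The case against.** The strongest reply is that the intent is plain. The parenthesis names the fall during therapy, the lead-in speaks of an immediate effect, and 7.5 plans blood pressure during each therapy. On that view the reference to a value afterwards is loose phrasing. This stands as evidence of intent, but the operative definition still says something else and should be brought into line.

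Other objections limit what may be claimed:

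- A reader might infer that 7.1 states that the final measurement follows the acclimatization break. It does not. It places that measurement before disassembly, and the rest is implied by the order of the text. Nor does 4.2.2 name the final measurement as its endpoint.
- In 4.2 the term intervention phase means the three weeks. If that sense applies, the fault is a missing time point, and the recovery illustration does not apply.
- A reader might infer that section 10 caps falls at 20 mmHg. It is a trigger for a lower angle: a fall can exceed 20 before the angle is reduced. The hard cut above is only a limiting case.
- A reader might infer that the upright fall goes unmeasured. The continuous recording contradicts that.
- Duration of verticalization and maximum tilt are also analysed, as co-variables, so blood pressure would not be read entirely alone.

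The exact replacement, such as a minimum, a mean or a last upright value, is a choice that an analysis plan could reasonably make. The protocol needs only to point at the upright phase.

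**Conclusion.** The point holds as a badly fixed definition of one secondary outcome. On none of the available meanings does the stated contrast target the upright fall that the hypothesis names. For the single-session meaning, this rests on taking the order of the text in 7.1 as the order of events.

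The size of the loss cannot be derived from the protocol. It depends on how much of a fall persists at horizontal and on measurement noise, and the documents give neither; the illustrative range runs from a complete loss of the difference to keeping half of it. The documents do not support the stronger conclusion that the trial cannot assess circulatory stabilization, because the needed readings are collected. CRS-R and the sample size are unaffected. The change should be made because it is cheap and prevents a null result from being misread.

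**What to change.** In 4.2.2, define the contrast as the horizontal reading on the device, before the leg drive starts and before uprighting, minus an upright reading from the continuous recording. One workable choice is the lowest value in a window common to both arms, for example from the start of uprighting through the first 15 minutes at the achieved angle (the minimum duration in 7.1), including any reading that triggers a step-down. Report the proportion of sessions with a step-down alongside. Keep the before/after pair as description and leave section 10 unchanged.

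**Cost.** A reworded sentence and slightly more data extraction. No new visit or device is foreseen, provided the recording interval, which the protocol does not state, is short enough to yield upright readings.

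**Downside.** Falls remain curtailed, though not strictly capped, by the step-down rule, and sessions stepped down or stopped early contribute a shorter window. The step-down proportion is reported for that reason.

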### 6.2.2 Randomized controlled trial

Fifty patients will be enrolled in this study.

Sample size calculation

The sample size was estimated according to the main criterium measured by CRS and based on a 6-week follow-up on the effect of the standard therapy in 12 minimally responsive/apallic patients. The differential value of the CRS before and after a 6-week standard therapy showed a mean value improvement of 6.5 points with a variance of 12.3 (SD=3.5). An additional improvement of the CRS by 3 points is expected as results of the study planned here. This means that on the average an additional improvement in half of the evaluated items of the CRS is expected.

The sample size was estimated in order to check by inference statistical means the hypotheses of an interval-scaled feature ([10]) if the prerequisite of a corresponding normal distribution is fulfilled. The values  $\alpha = 5\%$  two-sided, power = 80% result in a group size of 22 patients for each of the two groups with the expected increase of CRS by 3 points. A difference of at least 3 points between the

two groups can be established as significant in case of a variance of the differential values (before/after treatment) of the CRS of  $3.5^2 = 12.3$  and in group size of  $n=22$  with an error probability of 0.5 and a power of 0.8. In addition the number of therapy drop-outs was so determined that the required number of patients will still be achieved even after subtracting an expected drop-out rate of 10%. Thus, a total of 25 patients as group size is included in the randomization procedure.

A 2-way analysis of variance (ANOVA) will be performed to statistically analyse the primary outcome parameter CRS-R. If the assumptions of homogeneity of variances or normal distribution are disproven, nonparametric tests will be used.

In case patients withdraw from the study at the wish of the caretaker, the patient will be referred to in the log book as “intention-to-treat”.

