## **10 Termination criteria**

Individual

- If the systolic blood pressure falls by 20 mmHg or the diastolic blood pressure by more than 10 mmHg during the uprighting of the patient, therapy is continued at the next lowest tolerated angle of uprightness (30 or 50 degrees).
- The same procedure is followed with symptoms of a presyncope (tachypnoe, paleness, increased sweating...).
- Therapy is immediately terminated if the pulse falls below 40 beats/min or rises above 140 beats/min.
- Arterial hypotension (<80 mmHg).
- The occurrence of a new disease or complication of the primary illness that makes a continuation of the study impossible.
- Legal proxy withdraws participation agreement.

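### Duration of verticalization and maximum tilt are named as covariables for the circulation outcomes, although both are consequences of treatment and of the circulatory response; adjusting for them would typically attenuate the estimated Erigo effect

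*Protocol*

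**What the plan says.** Protocol section 4.2.2 lists heart rate, blood pressure and oxygen saturation as the measures of an immediate stabilizing effect on circulation. The last bullet of that list reads: "As co-variables the duration of verticalization (max. of 30 min per therapy session), and the degree of the maximum tilt will be analyzed". For blood pressure the hypothesis is that the "difference between initial value and the value after the intervention phase is greater for the tilt-table therapy". Duration and angle carry no hypothesis of their own.

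Elsewhere the protocol says how the two variables come about:

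- Section 4.1 (pilot aim) describes the expected circulatory advantage of the Erigo: "a prolonged mobilization in an extremely vertical position should be possible".
- Section 7.1 makes the top step conditional: "if circulation is good, to 70 degrees". On time it says: "The duration of mobilization in the indicated time period is as long as possible, if there is no depression of the circulation".
- Section 10 gives the trigger, "If the systolic blood pressure falls by 20 mmHg or the diastolic blood pressure by more than 10 mmHg during the uprighting", and its consequence: "therapy is continued at the next lowest tolerated angle of uprightness (30 or 50 degrees". Presyncope symptoms lead to the same step back.

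The only model named for the randomized trial is in section 6.2.2 and concerns another outcome: "A 2-way analysis of variance (ANOVA) will be performed to statistically analyse the primary outcome parameter CRS-R".

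**The concern.** A covariate in a randomized comparison should be fixed before treatment starts, or at least be untouched by it. These two are neither. The device is expected to change them, and the session rules tie them to the circulatory response that the outcomes are meant to capture.

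A patient who tolerates the session well goes higher and stays longer. One whose pressure falls is brought down. Comparing the arms at equal angle and equal duration therefore compares patients matched on tolerance, which is what the Erigo is supposed to improve. That contrast no longer has the protection of randomization, and part of the effect of interest is removed from it.

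At stake is the answer to the secondary question of circulatory stabilization. There is a second cost: because the angle gives way when pressure falls, part of any benefit will show as angle reached and time tolerated. The protocol labels these as covariables rather than as results.

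**Working it through.** **1. Scope.** The protocol states no figure for the circulation outcomes, so there is none to reproduce. Its sample size rests on the CRS alone: 2 × (1.96 + 0.84)² × 3.5² / 3² ≈ 21.4, rounded up to 22 per group, and 22 / 0.9 = 24.4, rounded up to 25. Nothing below changes that.

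**2. What depends on what, by the protocol's own rules.**

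| Link | Source |
|---|---|
| Arm → duration and angle | 4.1, expected benefit (stated for the pilot) |
| Circulation → maximum angle | 7.1, condition for 70 degrees; 10, step back after a pressure fall or presyncope |
| Circulation → duration | 7.1, 15 to 30 minutes as circulation permits |

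Both variables lie downstream of the arm. For blood pressure they also lie downstream of the outcome.

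**3. First illustration, angle only.** All inputs are assumed: mean systolic fall 8, 14 and 20 mmHg at 30, 50 and 70 degrees; patient SD 7; residual SD 4; step back at 20 mmHg; Erigo benefit 8 mmHg at 70 degrees.

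- SD of a single fall: √(7² + 4²) = √65 = 8.06.
- Tilt table at 70 degrees: P(fall < 20) = Φ(0) = 50%. Erigo: Φ(8 / 8.06) = Φ(0.99) = 84%. Requiring success at the earlier step as well lowers these slightly, to the simulated 48% and 83%, a difference of 35 points.
- Difference in fall at the final angle: 3.4 mmHg unadjusted and 3.1 adjusted for angle. The loss is 0.3 / 3.4 = 9%.
- Benefit 6: 2.3 to 2.1, a loss of 9%. Benefit 10: 4.9 to 4.4, a loss of 10%.

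The distance from 8 to 3.4 mmHg (4.6 mmHg) is already there without any covariate. It comes from the step-back rule, which cuts off large falls. Only the 0.3 mmHg belongs to the adjustment. The simulated differences also depend on details these inputs leave open, such as whether measurement error is redrawn after a step back and whether the benefit grows with angle. Re-running the same inputs under other choices of this kind gave larger losses, so about 10% is one illustration and not an estimate.

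**4. Second illustration, angle and duration.** Assumed: benefit 5 or 8 mmHg; slope 0.1 to 0.3 mmHg per degree; between-patient SD 6 or 12; residual SD 4; duration between 15 and 30 minutes, shorter with a larger fall. There were 24 scenarios with two measures of the fall, giving 48 comparisons.

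| Case | Unadjusted | Angle | Angle and duration |
|---|---|---|---|
| Benefit 5, slope 0.2, SD 12, effect scaled with angle | −3.4 | −2.5 | −1.0 |
| Smallest loss with both (benefit 8, slope 0.1, SD 6) | −7.95 | −7.32 | −5.61 |
| Largest loss with both (benefit 5, slope 0.3, SD 12) | −3.20 | −1.68 | −0.53 |

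With both covariates the estimate shrank in all 48 comparisons, from (7.95 − 5.61) / 7.95 = 29% to (3.20 − 0.53) / 3.20 = 83%. With angle alone it shrank in 45 and rose in 3; the largest loss was (3.75 − 1.33) / 3.75 = 65%. With no true treatment effect, adjustment produced no bias.

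**The case against.** The strongest reply is that adjustment is inferred. The bullet stands in a list of measured parameters under a heading for secondary outcomes, says only that the two variables will be analyzed, and names no ANCOVA or regression. A statistical analysis plan may settle the model. If the word means accompanying measures reported alongside the others, there is no bias and half of the fix is in place. This stands as a limit on the claim. It does not remove the point: the ordinary sense of a covariable is an adjustment term, and the text as written invites that use.

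Other objections also hold in part:

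- **Size.** A reader might infer that the real benefit is adjusted away, or that the drop from 8 to about 3 mmHg in the first illustration measures the harm done by the covariates. Neither is supported. Most of that drop is the step-back rule acting on the unadjusted comparison. The larger losses in the second set depend on an assumed link between fall and duration, whose direction follows section 7.1 but whose strength does not.
- **Which outcome.** A reader might infer that all three circulation outcomes drive the angle. Section 10 ties the angle to blood pressure and presyncope. It names no saturation trigger, and its pulse limits end the session rather than set the angle. For saturation and heart rate the argument is that the covariates are consequences of treatment; dependence of the angle on the outcome itself is documented only for blood pressure.
- **Which measurement.** Section 4.2.2 sets the initial pressure against the value after the intervention phase, yet speaks of a drop during therapy. The simulations model the fall while tilted, which is one reading.
- **Source of the expectation.** The passage on longer, more upright mobilization is the pilot aim. Section 4.2 carries the same parameters into the randomized trial, but does not repeat the hypothesis.

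**Conclusion.** The point holds as a conditional one. Section 4.2.2 names two post-randomization variables as covariables, and sections 4.1, 7.1 and 10 show that they follow from the arm and from the circulatory response. Used as adjustment terms, they would distort the treatment comparison, typically towards no difference.

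The amount is not fixed by anything in the protocol. Under assumed inputs it was about 10% for angle alone in one set, between a small rise and a 65% loss for angle alone in the other, and 29% to 83% for angle and duration together. The unadjusted comparison remains a valid randomized comparison of the two treatment strategies, though not one at equal angle.

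Only secondary outcomes are concerned. It should be corrected, but it does not threaten the trial's main result.

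**What to change.** Replace the bullet in section 4.2.2 with:

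*Duration of verticalization and maximum tilt angle are secondary outcomes compared between the groups over all monitored sessions, with patient as random effect. The main treatment comparisons of heart rate, blood pressure and oxygen saturation are not adjusted for them (the pre-session horizontal value may be adjusted for); any analysis adjusted for tilt or duration is exploratory.*

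A comparison at the common 30-degree step may be added as supportive. It takes place before the later steps separate the patients, but it tests the devices at the lowest tilt step and so should not replace the main comparison.

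The cost is two more secondary outcomes and a little extra analysis. No treatment rule changes. Two practical points follow. The measurement table in section 7.5 does not list angle or duration, so their recording should be added there. It also gives 9 monitored sessions, whereas section 6 implies 4 × 3 = 12; the two should be reconciled so that the set of monitored sessions is defined.
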